### 2.5 Outcomes

Primary outcomes are resilience and mental wellbeing. Secondary outcomes are positive affect, positive affect regulation and anhedonia.

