The Responses to Positive Affect scale, child version (RPA-C) (55–57) was used to assess positive affect regulation (secondary outcome). The RPA-C consists of items reflecting both dampening (e.g., “When you felt happy, how often did you think: ‘I don't deserve this'?”) and savoring responses (e.g., “When you felt happy, how often did you notice that you felt full of energy?”). All 17 items are rated on a 4-point scale ranging from 1 (*not at all*) to 4 (*very often*). The minimum total score a participant can get on the RPA-C is 17, the maximum is 68. There is evidence for good convergent and incremental validity and internal consistency for each scale is sufficient to good (Cronbach's alpha ranges from 0.72 to 0.86) in both children and (young) adults (55–57).

Symptoms of anhedonia (secondary outcome) were measured using the Leuven Anhedonia Self-report Scale (LASS, 2nd version) (58). All 12 items (e.g., “There were few things I looked forward to.”) are rated on a 5-point scale going from 1 (*completely untrue*) to 5 (*completely true*) with higher scores reflecting higher levels of anhedonia (total score: minimum = 12, maximum = 60). The total scale of the LASS has good internal consistency with a Cronbach's alpha value of 0.81 (58) and there is evidence for good convergent and discriminant validity in a sample of adolescents (31).

The Depression Anxiety Stress Scale (DASS-21) (59) was used to assess basic mental health to control for baseline differences in the training groups, and to explore the generalized effect of the PET program on levels of depressive symptoms and stress at post-training and at follow-up. The DASS-21 consists of 21 items (e.g., “I felt like my life had no meaning.”) that are rated on a 4-point scale going from 0 (*never*) to 3 (*almost always*), with 0 as a minimum total score, and 63 as a maximum total score. There is evidence for good construct and concurrent validity and good internal consistency of the subscales of the DASS-21 in both adolescent and adult samples, with Cronbach's alpha ranging from 0.79 to 0.94 (60, 61).

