### 2.8 Statistical analysis plan

All analyses will be completed in accordance with CONSORT standards. Intent-to-treat analysis will be used. Our primary and secondary outcomes will be analyzed using analysis of variance (mixed ANOVA) with time (pre, post, 2-month follow-up) as a within-subjects factor, and condition (PET, CREAT) as a between-subjects factor. Any baseline differences will be covaried in analyses.

To take into account the repeated measure nature of the study, group differences for the continuous variables at post-training and at follow-up will be tested via a mixed ANOVA model. A model with a main effect for time and for group (PET program vs. CREAT program), random effects for the dummy variables representing time clustered within individuals, and an interaction between time and group will be run to detect changes between groups for the primary and secondary outcomes. Follow-up independent samples *t-*tests will be calculated to examine group differences at post-training and follow-up time points. To correct for the inflated risk of a Type I error from multiple comparisons, Benjamini and Hochberg's (65) false discovery rate procedure will be applied to the main outcomes (i.e., primary and secondary outcomes). Although sample size planning was based on mixed ANOVA modeling, multilevel analyses that take into account the dependence in the data at school-level (clusters) will also be conducted to account for possible variance due to school membership.

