### 3.2 Dissemination plan

We plan to share consolidated findings in an article, which will be submitted for publication in a peer-reviewed journal. Furthermore, we plan to develop a free, online, web-based self-directed PET protocol for teachers if the study provides evidence that the PET program is effective in increasing adolescents' resilience and mental wellbeing, so teachers can deliver the program to future students without the need of professional external trainers.

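### One Benjamini-Hochberg procedure over primary and secondary outcomes makes significance on the two primaries depend on the secondary results

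*Protocol article*

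**What the plan says.** Section 2.5 separates the outcomes by rank: "Primary outcomes are resilience and mental wellbeing. Secondary outcomes are positive affect, positive affect regulation and anhedonia". That is two primaries and three secondaries.

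Section 2.8 gives the aim of the correction ("To correct for the inflated risk of a Type I error from multiple comparisons") and its scope: the Benjamini-Hochberg "false discovery rate procedure will be applied to the main outcomes (i.e., primary and secondary outcomes"). No separate primary family, order of testing or gatekeeping is stated. The same section plans a mixed ANOVA with a time-by-group interaction, and then t-tests: "tests will be calculated to examine group differences at post-training and follow-up time points". It does not say which of these tests enter the procedure.

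Section 3.2, like the abstract, makes the roll-out to teachers conditional: it follows "if the study provides evidence that the PET program is effective in increasing" resilience and mental wellbeing. Nowhere does the article say formally whether success needs both primaries or only one. Section 2.1 bases the sample size on an alpha of 0.05 and mentions no multiplicity adjustment.

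**The concern.** Naming two outcomes as primary normally means that the main claim stands or falls on them. A single step-up procedure over all outcomes removes that distinction at the point of decision. Suppose that resilience gives p = 0.03 and wellbeing is clearly not significant. With five outcomes, resilience is declared significant if all three secondaries are rejected and not significant if none is. The evidence on resilience is the same in both cases.

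False discovery rate control bounds the expected share of false claims in the whole set. It does not bound the chance of a false claim on a primary. Two things are at stake: some excess false-positive risk on the primaries when the affect measures respond and the primaries do not, and a loss of power on the primaries when the affect measures do not respond.

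**Working it through.** **Inputs.** Two primaries and three secondaries (section 2.5), so m = 5. Section 2.5.1 says "The RPA-C consists of items reflecting both dampening" and savoring responses. If these are scored separately, which is an assumption, m = 6. The false discovery rate level is taken as q = 0.05, the alpha of section 2.1; section 2.8 gives no level. There is one test per outcome unless stated otherwise. Tests are two-sided, and participants are treated as independent (class clustering is left out).

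**The plan's own figure.** Reading the effect size of 0.25 as Cohen's f (an assumption), a two-group F test with N = 128 has noncentrality 128 × 0.25² = 8.0 and power 80.1%. At N = 130 the power is 80.8%. The stated 130 is therefore reproduced as a single test at 0.05, with no allowance for multiplicity.

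**The moving bar.** Benjamini-Hochberg rejects the k smallest p-values, where k is the largest rank with p(k) ≤ kq/m. If s secondaries are rejected and the other primary is not, a primary needs p ≤ (s + 1) × 0.05/m.

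| | no secondary rejected | all secondaries rejected |
|---|---|---|
| m = 5 | 1 × 0.05/5 = 0.010 | 4 × 0.05/5 = 0.040 |
| m = 6 | 1 × 0.05/6 = 0.0083 | 5 × 0.05/6 = 0.042 |

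With Holm on the two primaries, the bar for a lone primary is 0.05/2 = 0.025, whatever the secondaries show.

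**Power at those bars.** For f = 0.25 (d = 0.5) and 65 per arm, the shift is 0.5 × √(65/2) = 2.85. In the normal approximation, power is Φ(2.85 − z), with z the two-sided critical value:
- bar 0.010: Φ(2.85 − 2.576) = 61%
- bar 0.025: Φ(2.85 − 2.241) = 73%
- bar 0.040: Φ(2.85 − 2.054) = 79%

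**False claim on at least one primary, both primaries null.** In the extreme case every secondary is certain to be rejected and the tests are independent. A claim then arises if the smaller primary p-value is at most 0.040, or if both are at most 0.05:
- m = 5: 1 − 0.96² + (0.05 − 0.04)² = 0.0784 + 0.0001 = 0.0785
- m = 6: 1 − (1 − 0.0417)² + (0.05 − 0.0417)² = 0.0817

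Simulation, with correlation between outcomes of 0 and 0.5, gives:

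| Secondaries | m = 5 | m = 6 |
|---|---|---|
| all null | 2.1–2.4% | 1.8–2.2% |
| 80% power | 5.3–6.5% | 5.3–6.7% |
| overwhelming | 7.3–7.9% | 7.6–8.2% |

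Holm on the pair stays at about 5% or below in every row.

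**If both primaries are required.** The largest possible bar is m × 0.05/m = 0.05, so a joint claim needs both p-values to be at most 0.05. Its false-positive rate therefore cannot exceed 5%. With both primaries null, it is 1% or less.

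**Power when the primaries are real and the secondaries null.** Starting from 80% unadjusted power, power per primary is 65–66% (m = 5) or 62–63% (m = 6), against 76–77% with Holm on the pair. Power to claim both with m = 6 is 44–51%, against 64–69% with each tested at 0.05 unadjusted.

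**The case against.** Much can be said for the plan.

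- **Choice of method.** False discovery rate control over a declared set is a recognised, prespecified method, and the article never promises family-wise control. A reader might infer that section 2.8 contradicts its own aim. It does not: it names the error rate it controls. This is a poor choice for the primaries, not an inconsistency.
- **Roll-out.** A reader might infer that the roll-out decision carries an inflated false-positive risk. The abstract and section 3.2 join resilience and wellbeing with an and. If that means both are needed, pooling cannot push the risk above 5%. This stands, although no formal rule is fixed.
- **Worst case.** The figure of about 8% needs both primaries exactly null and every secondary almost certain to be rejected. The article treats positive emotions as a route to resilience and wellbeing, so this is not the pattern it expects. The large effects cited in section 2.1 are for specificity and anticipated pleasure, which are not the listed secondary outcomes. With secondaries at d = 0.25 the rate is 2.9–3.8%. This stands.
- **Both time points.** A reader might infer rates of 10.5–14.1% by putting every post-training and follow-up test into one family. Section 2.8 does not say that these tests all enter.
- **Power.** Section 2.2 reports 188 participants, more than planned. After the 17% drop-out of section 2.1, about 188 × 0.83 = 156 remain. At d = 0.5 with the secondaries null, power per primary is then 74–77% under pooling. If all outcomes have real effects, pooling and Holm have similar power. The loss is therefore smaller at the achieved size, but it does not vanish.
- **Unseen detail.** The preregistration may define the family further. Even so, the published text states both the procedure and its scope, and one family is the natural reading.

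**Conclusion.** The point holds at moderate size. As written, significance on resilience or wellbeing depends on the secondary outcomes in both directions. The bar for a lone primary moves between 0.010 and 0.040 with the five listed outcomes, or between 0.0083 and 0.042 if dampening and savoring are separate outcomes.

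Error on the primaries exceeds 5% only if either primary alone supports a claim and the secondaries have real effects. Even then it is at most about 8% with one test per outcome. When everything is null, pooling is conservative for the primaries. The more general cost is lost power when the secondaries do not respond: about 65% (m = 5) or 63% (m = 6) per primary, against 77% with Holm.

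These figures assume q = 0.05, one test per outcome, independent participants and correlations between outcomes of 0 to 0.5. The simulated power loss also assumes 80% unadjusted power.

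**What to change.** Amend section 2.8 before analysis, with a date, so that it does the following:

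1. Treats the two primaries as their own family and states the success rule. If both must be significant, test each at 0.05 without adjustment; this matches the roll-out wording. If either suffices, use Holm at 0.05 on the pair.
2. States which test or tests per outcome enter: the time-by-group interaction, or the post-training and follow-up contrasts with an adjustment across them. Both time points in the hypotheses of section 1.2 can be kept.
3. Applies Benjamini-Hochberg only within the secondary outcomes, and says whether dampening and savoring count as one or two.

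The cost is about one paragraph and no new data. Strong secondary results could no longer help a primary over the line. Requiring both primaries has its own price: at 80% power each, joint power is 0.8 × 0.8 = 64% if they are independent and about 69% at a correlation of 0.5. Section 2.10 says that data collection is complete, so the published rule would change after the fact. The change must therefore be dated and disclosed in the results report.

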**Methods:**

A cluster randomized controlled trial with a 2 (condition) × 3 (time-point) factorial design was conducted. Classes of adolescents were randomized to either a PET program (intervention) or a CREAtive writing Training (CREAT) program (active control). Both trainings consisted of four sessions of 50 min (one session, weekly, for four consecutive weeks) and were delivered in schools. Before (pre-training, T1), immediately after (post-training, T2), and 2 months after the training (follow-up, T3), participants completed a series of self-report questionnaires. Primary outcomes are resilience and mental wellbeing. Secondary outcomes are positive affect, positive affect regulation and anhedonia. CONSORT criteria for conducting and reporting RCTs will be used.

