## 2 Materials and methods

### 2.1 Study design and sample size

A cluster randomized controlled trial with a 2 (condition; PET program vs. CREAT program) × 3 (time point; baseline, post-training, and follow-up) factorial design was conducted. Classes of adolescents were asked to complete measures of the study outcomes at all three time points (see procedure).

A total sample of 130 adolescents (i.e., *N* = 65 for each condition) provides 80% statistical power to investigate the effectiveness of the PET program, with an alpha of 0.05 and estimated medium effect sizes of 0.25 (38). Given previous (large) effect sizes ranging from *d* = 0.82 (for increased specificity) to *d* = 1.78 (for anticipated pleasure) (11, 14), this more conservative effect size estimate will help mitigate against Type II errors. However, in anticipation of considerable drop-out rates, some oversampling was done. We intended to recruit 15% extra participants (based on drop out of ±17% in previous school study of our lab), resulting in an sample size of approximately 150 participants (75 per group).

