### 2.2 Participants

Participants were recruited via secondary schools in Flanders, Belgium. Years 1 to 4 (1st and 2nd grade) of general secondary education were invited to participate, referring to ages 12 – 16. Five different schools (spread across three provinces) participated in the study. Each school selected one pair of parallel classes, which resulted in five pairs of classes (two of the first year, one of the second year, and two of the third year). In total, 188 adolescents participated in the study. Of all the adolescents, 95 were in the PET program (*M*_age_ = 13.2, SD_age_ = 1.00) and 93 in the CREAT program (*M*_age_ = 13.3, SD_age_ = 1.08). Gender distribution was approximately the same in both groups (PET program: 73.6% females, 25.3% males, 2.1% other; CREAT program: 76.3% females, 22.6% males, 1.1% other).

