Subsequently, participants completed the baseline assessment online, which consisted of a series of self-report questionnaires. It is only after completion of this first assessment that the researcher who was coordinating the study in the schools and who delivered the trainings was informed about the result of the random allocation (conducted by an independent statistician) of classes to one of the two conditions. The training programs started 1 week after the first assessment, and, in every school, classes received training sessions on the same days. Furthermore, training sessions were delivered by a researcher without a teacher being present. In that way, contextual variation across sessions and classes was kept to a minimum (e.g., no confounding effects related to the presence of a particular teacher). In addition, efforts were made to ensure that both trainings closely resembled in terms of format, structure, intensity, interaction between adolescents, invitations to practice with the skills taught during the in-class sessions. In this way, we aimed to prevent that adolescents would start to speculate about study hypotheses.

After completion of the trainings, adolescents of both groups took part in two final assessments. That is, a similar series of self-report questionnaires were presented 1 week (post-training) and, again, 2 months after the final training session (follow-up). Assessments in parallel classes (i.e., same school) were administered at the same day to minimize potential confounding effects by contextual factors. Per assessment, completing the self-report questionnaires took approximately 60–90 min. Self-report questionnaires were administered via Qualtrics (GDPR-proof online survey platform) on the laptop/tablet of the participants at school, with the intention to minimize errors due to manually entering data and missing values (i.e., “request response” option if questions were not completed). One of the involved researchers was present during the assessments, so participants could ask questions if necessary.

At the end of the study, participants will receive a €25-voucher for Bol.com (a local online store) as an incentive. In addition, participants and participating schools will be debriefed via email about our specific hypotheses and they will have the possibility to contact the researchers for additional information. Participating schools will automatically be informed about the general results.

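### Classes were randomised, but no stated analysis has a class term: the ANOVA and t-tests treat pupils as independent, and the added multilevel model clusters by school

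*Protocol article*

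**What the plan says.** The abstract states: "Classes of adolescents were randomized to either a PET program (intervention) or a CREAtive writing Training (CREAT) program (active control"). Section 2.3 likewise has an independent statistician allocating at random, and what is allocated is "of classes to one of the two conditions". Section 2.2 gives the number of clusters: "Each school selected one pair of parallel classes, which resulted in five pairs of classes". It also gives the number of pupils: "In total, 188 adolescents participated in the study", 95 in PET and 93 in CREAT.

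Section 2.8 then sets the main analysis: "Our primary and secondary outcomes will be analyzed using analysis of variance (mixed ANOVA"), with time within subjects and condition between subjects. The random effects it describes are for time within individuals. Independent-samples t-tests at post-training and follow-up come next, with a false discovery rate correction. The section acknowledges that the sample size was planned on the mixed ANOVA and adds that "multilevel analyses that take into account the dependence in the data at school-level (clusters) will also be conducted", to allow for variance arising from school membership. No analysis in the article contains a term for class.

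**The concern.** The class is the unit of randomisation and of group delivery. Pupils in a class share classmates, a training group and four sessions, so their outcomes may be correlated. Any class variance enters the difference between arms, and an analysis that omits it gives a standard error that is too small.

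The school model does not repair this. Parallel classes in a school are trained and assessed on the same days (section 2.3), so school acts as a matching factor. A school random intercept removes variance that both arms share and leaves out the variance that sets the error of the comparison.

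Both primary outcomes are affected. The false discovery rate procedure cannot help, because the p-values fed into it are already too small. Sections 2.8 and 3.2 together make the stake practical: evidence of effectiveness from these tests leads to a teacher-delivered online version of the programme. Agreement between the ANOVA and the multilevel model would look like reassurance and would be none.

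**Working it through.** **The plan's own figure.** Section 2.1 states: "A total sample of 130 adolescents (i.e., *N* = 65 for each condition) provides 80% statistical power", "with an alpha of 0.05 and estimated medium effect sizes of 0.25". Reading 0.25 as Cohen's f (d = 0.5), a two-group F test on independent pupils has non-centrality f²N = 0.0625 × 130 = 8.125 and power 80.8%; the smallest N reaching 80% is 128. So the 130 reproduces as an individual-level calculation with no design effect.

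**Inputs for the check.** Mean class size m = 188/10 = 18.8 (section 2.2). Alpha 0.05, taken as two-sided. The class ICC is not given, so 0.01 to 0.10 is assumed.

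**Pupil-level t-test.** Design effect DE = 1 + (m − 1) × ICC = 1 + 17.8 × ICC. The true standard error is √DE times the one reported. Real type I error = 2 × [1 − Φ(1.96/√DE)]. Effective sample size = 188/DE.

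| Class ICC | DE | SE ratio | Real type I error | Effective N |
|---|---|---|---|---|
| 0.01 | 1.18 | 1.09 | 7.1% | 160 |
| 0.02 | 1.36 | 1.16 | 9.2% | 139 |
| 0.05 | 1.89 | 1.37 | 15.4% | 99 |
| 0.10 | 2.78 | 1.67 | 24.0% | 68 |

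**School model, worked for one case.** Take 5 schools × 2 classes × 19 pupils, with variance shares of 0.02 for school, 0.05 for class and 0.93 for pupil, and each pair split between arms.
- True variance of the arm difference: 2 × (0.05 + 0.93/19)/5 = 0.0396, SE 0.199. The school share does not appear.
- Expected residual variance after fitting arm and school but not class: [4 × (0.93 + 19 × 0.05) + 180 × 0.93]/184 = 0.951.
- Variance the model reports: 2 × 0.951/95 = 0.0200, SE 0.141.
- The SE is short by a factor of 0.199/0.141 ≈ 1.41, so the real error is 2 × [1 − Φ(1.96/1.41)], about 16%.

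**Null simulation** (40,000 runs per row, same layout, school share 0.02), rejection rate at nominal 5%:

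| Class ICC | Pupil t-test | School random intercept | Paired class-level (4 df) |
|---|---|---|---|
| 0 | 4.8% | 5.0% | 5.0% |
| 0.01 | 6.8% | 7.1% | 4.9% |
| 0.02 | 8.9% | 9.3% | 5.0% |
| 0.05 | 15.8% | 16.6% | 4.9% |
| 0.10 | 24.3% | 25.8% | 5.0% |

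The school model is slightly worse than the t-test, because removing school variance shrinks a standard error that was already too small.

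**Time-by-group interaction.** Stable class differences cancel from change over time, and so do stable differences between pupils. If class-by-time variance is a share w of the total at each occasion and a pupil's scores correlate r between occasions, the ICC of change is w/(1 − r). With w = 0.01 and r = 0.5 (both assumed) it is 0.02, which by the first table gives 9.2%.

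**The case against.** Several points can fairly be made for the plan.

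- **The size of the class ICC is unknown.** At zero there is no inflation. One researcher delivered both programmes, no teacher was present, and both classes in a school were trained on the same days, all of which limits class variance. This stands as a limit on the figures. It does not justify assuming zero, because shared peers and group sessions remain.
- **School variance works the other way in the t-test.** Ignoring variance common to both arms makes that test conservative: with a school share of 0.10, simulated error was 4.2% at class ICC 0 and 5.8% at 0.01. The offset is negligible by a class ICC of 0.05, and it is absent from the school model.
- **The main test is the interaction.** Stable class effects drop out there, so the tabulated rates apply in full only to follow-up t-tests without baseline adjustment. This stands: for the interaction the ICC must be read as that of change.
- **The multilevel model's random structure is not fully specified.** With one class per arm in each school, class within school is the same term as school-by-condition, so a random slope for condition would carry the missing variance. But section 2.8 names school as the cluster and school membership as the purpose, and nothing in it points to such a slope.
- **Allocation within pairs is not stated outright.** The parallel classes and the 95 to 93 split make it likely. If pairs were not split, class would still be unmodelled.

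**Conclusion.** The concern holds. The article randomises classes, makes analyses that ignore class the main ones, and names the wrong level in its only clustered analysis. For any positive class-level variance in the contrast being tested, the school random-intercept model understates the standard error. The t-tests do so as well once class variance exceeds about 1/18 of school variance.

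For an assumed class ICC of 0.01 to 0.10, real error at nominal 5% is about 7% to 24% for the t-tests and 7% to 26% for the school model. These figures rest on about 19 pupils per class, pairs split between arms, a school model with a random intercept only and, for the interaction, an ICC of change in the same range. The direction of the error needs only that class-level variance is not negligible. This must be corrected before the primary results are interpreted.

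**What to change.** Make one clustered model primary. Fit school as a fixed effect (the five pairs) and class as a random effect, add class-by-time if T2 and T3 are modelled jointly, adjust for baseline, and use Kenward-Roger or Satterthwaite degrees of freedom (about 5 − 1 = 4). The equivalent alternative is a paired analysis of the five within-school differences in baseline-adjusted class means. That version also avoids the difficulty that a class variance estimated from so few classes can come out at zero. Confirm from the allocation record that each pair was split.

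In section 2.8, name class as the level of clustering, stratified by school, in place of school. Report the class ICC for each primary outcome. Draw no inference from the unclustered ANOVA and t-tests. Date the change and record it before outcomes are compared by arm.

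Only analysis wording changes: class and school are already recorded (section 2.7). The price is precision. For d = 0.5 with 188 pupils, power is 93% if independence is assumed. On 4 degrees of freedom it is 66%, 60%, 47% and 35% at class ICC 0.01, 0.02, 0.05 and 0.10, before any gain from school blocking or baseline adjustment. With data collection complete (section 2.10), more classes cannot be added, so the report should state this limit.
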